## Abstract

**Introduction:**

Huntington’s disease (HD) is an inherited neurodegenerative disease causing progressive cognitive and motor decline, largely due to basal ganglia (BG) atrophy. Rhythmic training offers promise as therapy to counteract BG-regulated deficits. We have developed HD-DRUM, a tablet-based app to enhance movement synchronisation skills and improve cognitive and motor abilities in people with HD. This paper outlines a randomised controlled unblinded trial protocol to determine the feasibility of a larger effectiveness trial for HD-DRUM. Additionally, the trial investigates cognitive and motor function measures, along with brain microstructure, aiming to advance our understanding of the neural mechanisms underlying training effects.

**Methods, design and analysis:**

50 individuals with HD, confirmed by genetic testing, and a Total Functional Capacity (TFC) score of 9–13, will be recruited into a two-arm randomised controlled feasibility trial. Consenting individuals with HD will be randomised to the intervention group, which entails 8 weeks of at-home usage of HD-DRUM or a usual-activity control group. All participants will undergo cognitive and motor assessments, alongside ultra-strong gradient (300 mT/m) brain microstructural MRI before and after the 8-week period. The feasibility assessment will encompass recruitment, retention, adherence and acceptability of HD-DRUM following prespecified criteria. The study will also evaluate variations in cognitive and motor performance and brain microstructure changes resulting from the intervention to determine effect size estimates for future sample size calculations.

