### Secondary objectives

To gain estimates of variability and absolute change before and after 8 weeks of HD-DRUM compared with usual-activity control in the following measures:

Performance measures in cognitive and motor tasks for sample size calculations for a future RCT.The means of grey and WM microstructure in BG and cerebellar brain networks^3^ to explore the neural mechanisms that underpin any training effects.The means of performance measures in cognitive and motor tasks and of grey and WM microstructure in BG and cerebellar brain networks^3^ to inform about disease-specific neural mechanisms including compensatory processes.

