### Trial design

We will conduct a two-arm randomised controlled feasibility trial of individuals with HD randomised to 8 weeks of HD-DRUM intervention or usual-activity control (figure 1).

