#### Outcome assessments

##### Primary feasibility outcome assessments

Recruitment will be measured as the number of participants assessed for eligibility, eligible, approached and consented to the study. Reasons for not approaching or enrolling eligible participants will be recorded on a screening log.Retention will be measured by the number of participants who complete the study after attending the follow-up visit after 8 weeks. Reasons for withdrawal and loss to follow-up will be recorded where possible.Acceptability will be measured with a semiquantitative self-report questionnaire on rating how easy the training was to use, how engaging it was, appropriateness of frequency, duration and difficulty, perceived beneficial or detrimental training effects, as well as likes, dislikes and potential improvements within the app. This will inform about any further app adjustments required to address the needs of people with HD for a future RCT.Adherence to the training will be automatically tracked within HD-DRUM by recording the frequency and duration of training sessions.

Feasibility success criteria have been predefined according to the following traffic lights system: green (all feasibility rates ≥70%) will signal that the trial was successful, amber (no rates below 40% but at least one below 70%) that the project requires review and design changes and red (at least one rate <40%) that a future RCT will not be feasible.

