### Sample size

Following the Consolidated Standards of Reporting Trials (CONSORT) statement extension to randomised pilot and feasibility trials,^40^ no formal power calculations have been conducted. We aim to recruit 50 individuals with HD. This number is pragmatic given the size of the target population, level of engagement required and resources available. It will allow estimation of recruitment, retention and adherence rates with a 95% binomial CI of no more than plus or minus 15 percentage points irrespective of the point estimate.

The combined population of the participating patient identification centres (PICs) should be adequate to achieve recruitment target, but this assumption will be tested as part of the feasibility assessment. While there is facility to add more PICs, further strategies to enhance recruitment will not be used within this feasibility trial.

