### Statistical methods

The study will be reported in accordance with the CONSORT statement extension to randomised pilot and feasibility trials.^40^ As this is a feasibility trial, it is not formally powered to test for effectiveness of the intervention while controlling type I error. The primary aim is to assess the feasibility. For this purpose, recruitment, retention and adherence rates and acceptability rating scores and thematic responses will be documented and evaluated according to the success criteria described above. Feasibility percentage rates will be calculated as follows:

Recruitment rate=100×(number of participants consented/number of participants eligible and approached) %.Retention rate=100×(number of participants completing the study at 8-week follow-up/number of participants consented) %.Adherence rate (frequency)=100×(number of days app used for training/40 days) %.Adherence rate (duration)=100×(number of minutes app used for training /(40 days×11.3 min average session duration=451 min) %.

Descriptive summaries such as mean and SD estimates (for continuous variables) of effect sizes and 95% CIs will be calculated for all secondary clinical and MRI outcome measures. Motor and mood measurements are detailed in the outcome section above and information about the cognitive and MRI outcome measures can be found in tables2  3. Differences in mean and SD of participants’ absolute and percentage changes from baseline will be calculated to provide estimates of effect size and variability of any performance changes in the two groups. All calculations will be conducted in SPSS^43^ and R.^41^ This will provide information to help estimate the sample size required for a future definitive RCT into HD-DRUM in this patient population. Note that the absence of a change in individuals with HD in the HD-DRUM group compared with the control group may suggest a beneficial effect of the intervention as HD is a progressive neurodegenerative disease.

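### The observed between-arm effect is planned as an input to the definitive trial's sample size, but about 25 per arm estimates it too imprecisely to serve as the target difference; the SD can be carried forward

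*Protocol article*

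**What the plan says.** Three places in the protocol article state the purpose.

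- Abstract (Methods, design and analysis): cognitive, motor and MRI changes are evaluated "to determine effect size estimates for future sample size calculations".
- Secondary objectives: the aim is "To gain estimates of variability and absolute change before and after 8 weeks of HD-DRUM compared with usual-activity control", and the first listed use is "Performance measures in cognitive and motor tasks for sample size calculations for a future RCT".
- Statistical methods: after describing mean and SD of change in the two groups as estimates of effect size and variability, the text says "This will provide information to help estimate the sample size required for a future definitive RCT into HD-DRUM in this patient population".

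On size, the Sample size section says "We aim to recruit 50 individuals with HD" and calls the number pragmatic. Its only numerical support is the precision of the feasibility rates. Statistical methods acknowledges that effectiveness is not powered and plans 95% CIs for all secondary outcomes. The article states no precision for the effect sizes.

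**The concern.** A sample size needs two kinds of input: nuisance quantities (SD, correlation, attrition) and a target difference. A pilot of this size estimates the first kind tolerably and the second poorly. The required sample varies with the inverse square of the target difference, so an error in that difference is magnified. A chance overestimate gives an RCT that is too small. A chance null or negative estimate could lead to a useful intervention being abandoned. Because all three passages name the effect or the absolute change as an input, this is a stated use and not a detail left out of a condensed article.

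**Working it through.** **Inputs from the article.** Total 50 (Sample size). Two arms (Trial design): "two-arm randomised controlled feasibility trial of individuals with HD randomised to 8 weeks of HD-DRUM intervention or usual-activity control". The retention limit for a favourable result is 70% (Primary feasibility outcome assessments): "green (all feasibility rates ≥70%) will signal that the trial was successful".

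**Assumptions, not in the article.** 1:1 allocation, so 25 per arm. Dropout from 0% to about 30%, so 25 down to 18 per arm. True standardised effect d from 0.2 to 0.8. Future RCT at two-sided 5% and 80% power.

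**1. The plan's own figure.** For a proportion with denominator 50 the widest Wald half-width is 1.96 × √(0.25/50) = 13.9 percentage points; the exact (Clopper-Pearson) half-width is 14.5. The stated ±15 points is reproduced. It concerns rates only and says nothing about effect sizes.

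**2. Precision of the observed effect.** SE(d) = √(2/n + d²/4n).

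- 25 per arm, d = 0.3: √(0.08 + 0.0009) = 0.284, half-width 1.96 × 0.284 = 0.56.
- 22 per arm, d = 0.3: SE 0.303, half-width 0.59.
- With t quantiles and d near zero: ±0.57 at 25 per arm, ±0.64 at 20, ±0.68 at 18.

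An observed d of 0.3 with 25 per arm has a 95% CI of −0.26 to 0.86 (noncentral t). The sample size per arm for 80% power, 2 × (2.80/d)², is 393, 175, 63 and 25 for d = 0.2, 0.3, 0.5 and 0.8. An observed 0.3 cannot tell these designs apart.

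**3. Consequence if the observed effect is used directly.** Size the RCT as N = 2 × (2.80/d_obs)² per arm. True power falls below 50% when d × √(N/2) < 1.96, that is, when d_obs > (2.80/1.96) × d = 1.43 × d.

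For d = 0.3 and 25 per arm:

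- The threshold is 1.43 × 0.3 = 0.429.
- P(d_obs > 0.429) = P(Z > 0.129/0.284) = 0.325.
- P(d_obs > 0) = 0.854.
- The share among positive pilots is 0.325/0.854 = 38%.

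The same steps for each true effect, checked by 200,000 simulated pilots with estimated SD:

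| True d | Observed effect ≤ 0 | True power < 50%, among positive pilots | Same event, share of all pilots |
|---|---|---|---|
| 0.2 | 24% | 50% | 38% |
| 0.3 | 15% | 38% | 33% |
| 0.5 | 4% | 24% | 23% |
| 0.8 | under 1% | 12% (formula) to 14% (simulation) | 12% to 14% |

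With 20 per arm the third column becomes 54%, 42%, 27% and 16%. With an RCT sized for nominal 90% power and 25 per arm it is 43%, 29%, 14% and 5%.

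**4. Precision of the SD.** With 48 df the 95% CI of the pooled SD is 0.83 to 1.25 times the estimate. The upper one-sided 80% limit is √(df/χ²₀.₂₀):

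- 48 df (25 per arm): √(48/39.62) = 1.10, squared 1.21.
- 42 df (22 per arm): √(42/34.16) = 1.11, squared 1.23.

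The future sample size scales with the square of the SD, so this allowance costs 21% to 23%.

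**The case against.** The strongest reply is that the article fixes no sizing rule. Statistical methods says only that the results will help to estimate the future sample size, and it lists variability beside effect size. The Secondary objectives put variability first. Nothing rules out a minimally important difference, and the definitive trial's sample size will be justified in its own protocol. SDs, retention and effects with 95% CIs are already planned outputs. The primary objective and the traffic-light decision do not use effect sizes at all.

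Most of this stands, and it limits the point. A reader might infer that the next RCT's power would usually be wrong. The article does not support that, because it would require a rule that takes the point estimate as it comes. A reader might also infer that, with so many cognitive, motor and MRI measures, the outcome with the largest effect will be chosen and its effect inflated by selection. The article neither states nor excludes such a choice, and many listed scores, such as error counts and control conditions, are not realistic primary outcomes. The case here does not rest on selection: imprecision alone makes it, even for a single outcome.

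What the reply does not remove is the stated purpose. The abstract says without qualification that effect sizes are wanted for sample size calculation. A CI that is reported but given no role in the calculation does not protect it.

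**Conclusion.** The point holds as a cheap improvement. The article plans to let the observed between-arm effect, as well as the variability, inform the definitive sample size. At about 25 per arm that effect has a 95% CI of about ±0.55 to ±0.6 SD, and is unreliable if taken directly as the target difference.

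The size of the harm depends on the true effect, which the article does not give. It is large for true effects of 0.2 to 0.3 and modest at 0.8. It also depends on 1:1 allocation, on completion (fewer completers make it worse), and on the future trial using the point estimate. No result of the present trial becomes invalid, and estimating the SD from it is sound.

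**What to change.** Reword the abstract, the Secondary objectives and the Statistical methods so that:

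- this trial supplies, for the future calculation, the SD of each candidate outcome with an allowance for its imprecision (for example an upper one-sided confidence limit), the baseline-to-follow-up correlation and the retention rate;
- the future target difference rests on a minimally important difference set independently of these results;
- between-arm effects are reported with 95% CIs as descriptive only.

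The cost is wording; no assessment or procedure changes. If the upper 80% limit of the SD is used, the future sample size is about 21% to 23% larger (25 to 22 per arm) than one based on the SD point estimate. The choice of limit is a convention, and another level would serve if stated.

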**Ethics and dissemination:**

The study has received favourable ethical opinion from the Wales Research Ethics Committee 2 (REC reference: 22/WA/0147) and is sponsored by Cardiff University (SPON1895-22) (Research Integrity, Governance and Ethics Team, Research & Innovation Services, Cardiff University, [name]). Findings will be disseminated to researchers and clinicians in peer-reviewed publications and conference presentations, and to participants, carers and the general public via newsletters and public engagement activities. Data will be shared with the research community via the Enroll-HD platform.

**Trial registration number:**

ISRCTN11906973.

STRENGTHS AND LIMITATIONS OF THIS STUDYHD-DRUM is a remotely accessible, tablet-based training tool that can be used at home and allows the objective assessment of adherence and training effects.The use of gamification to match users’ practice to a level appropriate to their abilities is expected to increase adherence and acceptability of HD-DRUM by avoiding frustration and boredom due to overchallenge and underchallenge.This trial will assess the feasibility of a future fully powered effectiveness randomised controlled trial and any modifications that may need to be implemented in HD-DRUM.The randomised controlled study design will allow the estimation of training-induced variability of changes in clinical and brain imaging measures, using state-of-the-art ultra-strong gradient 3T MRI.Due to the nature of the intervention and limited resources, researchers and participants are not blinded to group allocation.

## Introduction

### Background and rationale

 Huntington’s disease (HD) is a genetic neurodegenerative disease that leads to the progressive loss of cognitive and motor abilities, largely due to atrophy in the basal ganglia (BG)^1^ and other brain regions including the prefrontal cortex and frontostriatal connections.^2 3^ Striatal atrophy^1^ and microstructural alterations in white matter (WM) connections^2^ with associated cognitive control dysfunctions^3^,^5^ occur many years before the clinical onset of motor symptoms and will eventually negatively impact a person’s ability to live independently.^6^

Currently, there are no disease-modifying treatments for HD and symptomatic therapies are limited with significant side effects.^7 8^ There are no HD-specific cognitive interventions and only very few studies have investigated cognition-oriented interventions in people with HD.^9^

Rhythmic auditory stimulation (RAS) is a form of neurological music therapy^10^ that uses rhythmic beats as external cues to trigger movements.^11^ RAS has been found to improve gait and mobility in people with Parkinson’s disease (PD)^11^,^13^ and holds potential as an intervention for improving attention and executive functions.^12 14^ While PD and HD are clinically distinct diseases, they are both associated with BG neurodegeneration and deficits in interval timing and spontaneous rhythm generation.^15^ The BG is considered to play a key role in the prediction of upcoming events by internally generating temporal pacing signals.^16^,^18^ Together with the cerebellum and cortical areas involved in sensory, motor and attention processing, they form an extended network of brain regions that supports rhythmic sensory processing and movement generation.^16^ RAS interventions are proposed to work by compensating for the loss of BG-generated timing and rhythm signals with external rhythmic cueing.^11^ However, the actual neural mechanisms of rhythmic processing as well as the clinical effects of RAS interventions in people with HD remain unknown.

Previously, we explored 8 weeks of bongo drumming (~15 min five times per week) as a therapeutic tool for people with HD.^19 20^ We observed performance improvements in executive function tasks and changes in WM microstructural measurements of callosal and cortico-putamen connections.^19 20^ Although these initial pilot results were promising, they were preliminary in nature and necessitate validation through a fully powered randomised controlled trial (RCT). This study aims to investigate the feasibility of a larger RCT, as well as to explore any indicative effects and the neural mechanisms that may be responsible for potential clinical advantages associated with RAS.

For this purpose, we have codesigned with people with HD, a tablet-based RAS training application (app) (HD-DRUM)^21^ that is suitable for clinical evaluation because it allows the accurate quantification of training progression and adherence and uses gamification to match individual performance levels to training difficulty with the aim to increase acceptability. As HD-DRUM can be used at home it holds the potential of expanding intervention delivery to greater participant numbers for an effectiveness trial.

Here, we describe the protocol of an RCT to determine the feasibility of a larger effectiveness RCT into the clinical effects of HD-DRUM in people with HD. The trial will also explore training-induced changes in cognitive and motor functions as well as in MRI measures of morphology and microstructure of cortical and subcortical brain regions involved in rhythmic processing (BG, cerebellum, auditory and motor cortices). The clinical and neural effects of 8 weeks of HD-DRUM will be compared with a usual-activity control group in people with HD that will allow us to explore whether HD-DRUM can improve on current practice.

HD-DRUM has the potential to be a future training tool for slowing cognitive and motor decline in people with HD, alongside candidate disease-modifying treatments that are currently under consideration. Even a small delay in disease progression would translate into direct benefits for the quality of life of patients and their families.

### Primary objective

To assess the feasibility of a larger effectiveness RCT investigating 8 weeks of at-home HD-DRUM intervention compared with usual activities in people with HD.

### Secondary objectives

To gain estimates of variability and absolute change before and after 8 weeks of HD-DRUM compared with usual-activity control in the following measures:

Performance measures in cognitive and motor tasks for sample size calculations for a future RCT.The means of grey and WM microstructure in BG and cerebellar brain networks^3^ to explore the neural mechanisms that underpin any training effects.The means of performance measures in cognitive and motor tasks and of grey and WM microstructure in BG and cerebellar brain networks^3^ to inform about disease-specific neural mechanisms including compensatory processes.

### Trial design

We will conduct a two-arm randomised controlled feasibility trial of individuals with HD randomised to 8 weeks of HD-DRUM intervention or usual-activity control (figure 1).

**Figure 1 F1:**
[figure not shown]
Schematic overview of the two-arm randomised controlled feasibility trial. CUBRIC, Cardiff University Brain Research Imaging Centre; HD, Huntington’s disease; TFC, Total Functional Capacity.

## Methods

### Patient and public involvement

This study was developed with members of HD Voice, the patient and public involvement (PPI) group of the UK HD Association (HDA). PPI members are involved in the management and oversight of the study as members of the study management and steering groups. The HD-DRUM intervention was codesigned with people with HD. PPI members will contribute to the interpretation and the dissemination of the study findings.

### Participants, interventions and outcomes

#### Study setting

Participants will be identified, approached and recruited via specialist HD clinics in the UK. All baseline and follow-up clinical and MRI assessments will take place at the Cardiff University Brain Research Imaging Centre (CUBRIC). Participants will engage individually with the HD-DRUM intervention at home.

#### Recruitment

Eligible individuals will be identified by their clinician during their annual visit. Individuals interested in the trial will receive the patient information sheet (PIS). They will be asked to provide consent for the researchers to contact them to find out if they wish to proceed with the study. If they decide to participate, during their first appointment at CUBRIC they will be asked to provide informed written consent and complete the study assessments. Participants will be reimbursed for their travel expenses and any overnight accommodation.

The study will also be advertised on posters in clinic waiting rooms and via newsletters and websites of Health and Care Research Wales (HCRW) and the HDA UK. In these instances, interested parties must first contact one of the participating HD centre teams for further information.

#### Eligibility criteria

Participants will be eligible to take part in the study if they meet all of the inclusion criteria and none of the exclusion criteria.

#### Inclusion criteria

Individuals over the age of 18 years with a good command of the English language who fulfil the following criteria:

Premanifest or manifest HD as confirmed by genetic testing for the presence of the mutant huntingtin allele.A Unified Huntington’s Disease Rating Scale (UHDRS) TFC^22^ score between 9 and 13.Who participate in the Enroll-HD^23^ observational study (former Registry) (REC no 04/WSE05/89) or in routine clinical assessment of their TFC score.

